**A.2 SUMMARY**

Explain why this study is being conducted, using lay terminology.

*Guidance note:*

*Please convey what you think is the importance of the research and WHY it is being carried out.*

The national average for the percentage of women who go to at least on antenatal care (ANC) clinic in Uganda is close to 95%, but in the Kabale region we think it is closer to only 60%. This is thought be a result of isolated mountainous topography of villages combined with a deep mistrust of the governmental healthcare system compounded by a high reliance on traditional healers. It is well known that screening of women who are pregnant can help to detect problems that could affect the mother’s health as well as be a risk to the unborn baby. Many of these problems are treatable and some are curable, which could help the mothers and infants health. We plan to entice pregnant women on testing for HIV, syphilis, Hepatitis B, anemia (low blood count) by offering a free portable obstetric ultrasound (fOBU). If the women are found to have any of these conditions they will be provided with the appropriate management free of charge as per Ugandan Ministry of Health Guidelines.

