**A.4 METHODOLOGY**

Outline how you intend to achieve the objectives of the study.

*Guidance notes:*

*For each objective/hypothesis:-*

- *define the target population*
- *describe how the sample(s) is(are) to be recruited from the target population(s)*

*Even if the main thrust of the research is biomedical, the rationale behind your use of social science methods (e.g. patient interviews) should be clear.*

We intend to achieve the objectives of our study through two different research aspects, one focusing on non-clustered randomization (sample size of 288) and other looking specifically at randomized clusters (sample size of 550). We have clustered at the community level to observe for an effect of fOBU on increasing overall ANC attendance. We have randomized at the patient level for assessment of the efficacy of medical/dental outreach with fOBU to change patient preference for delivering in a health care center.

Communities in the Kabale District will be assessed for population size, demographics and birth rate. Communities that have similar characteristics will be selected and contacted to engage in the study. Communities who agree to participate in this study will be contacted and community leaders will make announcements at local schools, churches, and community events regarding the upcoming free antenatal clinics. During these announcements the community will be told either a) that there will be structured maternal health camps (sMHC) offering free obstetric ultrasound (OBU) or b) that there will be sMHCs with no mention of the fOBU. In actuality, to assure that all women are given the benefit of optimal care, all SMHCs will provide fOBU, but only the advertising messages will differ between groups. Communities will be stratified by catchment population (small, medium or large) prior to randomization and assignment to the intervention or control group. Additionally, we will be collecting demographic data on registration to clinic and asking a pre clinic questionnaire to assess maternal feelings towards the healthcare system, and their preferences for where to deliver their baby (at a healthcare center or at home).

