Sample size calculations were considered for two of the primary outcomes. For the first outcome – looking to determine the efficacy of portable ultrasound in improving maternal uptake of antenatal care due to portable ultrasound being offered – a simple randomization based on communities will be utilized. For the additional outcome of eliciting a change in patient preference for delivering at a healthcare facility before and after a rural outreach clinic the communities will be both clustered and randomized. In this case a design effect is added to account for the clustering for this patient-level outcome.

1. Facility based uptake of ANC (no clustering): At a two-sided alpha of 0.05 and holding power at 80%, with p1 of .70 and p2 of 0.52 [1], then 144 pregnant women will be required in each of the control and intervention groups. Inflating this by 25% to prepare for any non-consent and/or non-response, the required sample increases to 180 women per group. From experience gained in our pilot study, we anticipate that health facilities will enroll a greater number of women, therefore our sample will provide more than adequate power. We will conduct power calculations during analysis, however, we anticipate power of greater than 90%.
2. Patient-level outcomes (clustered): At a two-sided alpha of 0.05 and holding power at 80%, using an estimated intracluster coefficient (ICC) of 0.1 [2], with p1 of 0.95 and p2 of 0.85, and an average cluster size of 60 pregnant women (m), then 225 pregnant women will be required per study arm, which is equivalent to needing 4 clusters per group. Inflating this by 25% to account for potential non-response gives 282 pregnant women per group.

Notes:

1. Rate of uptake of antenatal care (at least 1 ANC visit) in pilot studies in our community
2. Generally, ICCs are not known prior to study start. For ICC assumption, it is generally accepted that clinical outcomes have ICCs of around .05; whereas process outcomes (which our research is studying) range from 0.05 to 0.15; we have used 0.1 in our calculations.

Reference: <http://www.who.int/reproductivehealth/topics/best_practices/intracluster_correlation.pdf>

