**1. Background**

According to statistics provided by the World Health Organization, Uganda currently has the 20^th^ highest rate of maternal mortality, and the 15^th^ highest rate of infant mortality in the world.^1^ Amongst nations in Africa, Uganda has one of the highest population growth rates, with an annual increase in 3.2% and a fertility rate of 6.7%.^1^ With approximately 1.5 million pregnancies/year, it is estimated that nearly 6000 women will die due to pregnancy related complications (16 mothers/day) – numbers which are exacerbated by poverty, malnutrition, illness, and lack of access to antenatal, peri-natal and postnatal health care services.

While maternal and child mortality is prevalent nationwide, the situation is particularly problematic in remote rural regions such as Kabale, which is located in southwestern Uganda. In contrast to the urban regions of Uganda where it is reported that close to 95% of women attend at least one antenatal care clinic (ANC)^2^ prior to delivery , current data points to only 66% presenting for ANC in rural Kabale^3^. Additionally, compared to nearly 60% of women delivering in health centers in urban areas, only 30% of births in Kabale take place in health centers, with most births occurring at home.^3,4^

Extreme poverty and malnutrition amongst women in the region have led to high rates of anemia – studies indicate that 64% of pregnant or new mothers are suffering from anemia in Kabale – in addition to high rates of HIV and malaria. As a result, 70% of the population who deliver at home in the Kabale region, are attended only by unqualified midwives who lack the necessary training and equipment to respond to high-risk delivery complications, are facing the risk of experiencing severe bleeding (caused by post-partum hemorrhage), infection (mostly after delivery), hypertensive disorders (eclampsia), obstructed labor, and ultimately, death.^4^

There are multiple contributing factors that are preventing pregnant women living in the Kabale region from receiving maternal healthcare services from trained professionals. These include cost, access, infrastructure, and cultural attitudes.

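### A.5.4 item 1: 0.70 v 0.52 needs 115 women per group, not 144, and the uptake total is 288 in A.4 but 360 in A.5.4

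*Protocol*

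**What the plan says.** - **Uptake calculation (Protocol A.5.4, item 1).** At two-sided 0.05 and 80% power, with no clustering, the item states: "with p1 of .70 and p2 of 0.52 [1], then 144 pregnant women will be required in each of the control and intervention groups". A 25% allowance is then added and "the required sample increases to 180 women per group". The item expects more women than this to enrol and anticipates power above 90%.
- **Source of the rate.** The note attached to 0.52 credits it to pilot studies in the investigators' community and defines uptake as at least one antenatal visit.
- **Totals (Protocol A.4).** The two components are described as "one focusing on non-clustered randomization (sample size of 288) and other looking specifically at randomized clusters (sample size of 550"). The A.5.1 table also shows 550 women.
- **Clustered outcome (A.5.4, item 2).** "Inflating this by 25% to account for potential non-response gives 282 pregnant women per group", which is 564 in total.
- **Uptake elsewhere.** A.2 says "in the Kabale region we think it is closer to only 60"%. Section 1 (Background) says "current data points to only 66% presenting for ANC in rural Kabale".

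**The concern.** Item 1 supplies everything a two-proportion calculation needs: both rates, alpha, sidedness, power and equal groups. The result should therefore be reproducible, and it is not. The 144 is about 25% above what the inputs give, which is too large a gap for rounding or choice of formula. It is also the size of the allowance added in the next sentence.

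The uptake component then has two totals, 288 and 360, and which one is right depends on how the 144 arose. A.8 makes the number of women presenting for care the primary objective, so this calculation sizes the main comparison. Any later multiplication by a design effect would carry the error forward.

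The control rate adds a softer question. The protocol gives 52%, about 60% and 66% for closely related quantities and does not say how they fit together. The sample size depends heavily on which one applies and on whether the target of 70% moves with it.

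**Working it through.** **Inputs (A.5.4 item 1):** p1 = 0.70, p2 = 0.52, two-sided alpha 0.05 (z = 1.960), power 80% (z = 0.842), 1:1 allocation, no design effect.

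**1. Reproducing the stated n.** Standard formula, with p̄ = (p1 + p2)/2:

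n = [1.960 √(2p̄(1−p̄)) + 0.842 √(p1(1−p1) + p2(1−p2))]² / (p1−p2)²

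- p̄ = 0.61; 2p̄(1−p̄) = 0.4758; p1(1−p1) + p2(1−p2) = 0.21 + 0.2496 = 0.4596
- n = (1.352 + 0.571)² / 0.18² = 3.696 / 0.0324 = 114.1, so **115 per group**
- With continuity correction: 124.9, so **125 per group**

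Other variants at the same alpha and power: unpooled variance 112, fully pooled variance 116, arcsine 114, Fisher's exact test about 120 to 124. At 90% power the formula gives 153. The only standard variant tried that comes close is 85% power with continuity correction (142), which contradicts the stated 80%. The 144 is not reproduced.

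**2. Where 144 could come from.**

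- *Allowance already included:* 115 x 1.25 = 143.75, so 144. The step to 180 (144 x 1.25) then applies the 25% twice.
- *Different control rate:* 0.70 v 0.54 gives 3.668 / 0.16² = 143.3, so 144. The value 0.54 appears nowhere in the protocol.

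**3. Totals for uptake.** 2 x 144 = 288 (A.4). 2 x 180 = 360 (A.5.4 after inflation). A.5.4 labels 144 as the number before inflation, so by that label A.4 omits the allowance. If 144 already includes it, A.4 is right and A.5.4 is wrong.

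**4. Power on the stated rates, ignoring clustering.** Power = Φ{[(p1−p2)√n − 1.960√(2p̄(1−p̄))] / √(p1(1−p1) + p2(1−p2))}

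| Rates | 115 per group | 144 per group | 180 per group |
|---|---|---|---|
| 0.70 v 0.52 | 80% | 88% | 94% |
| 0.70 v 0.54 | 71% | 80% | 88% |

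At 180 per group, power above 90% holds with 0.52 but not with 0.54.

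**5. Sensitivity to the control rate, ignoring clustering.**

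| Control rate | Target rate | n per group for 80% power | Power at 144 per group |
|---|---|---|---|
| 0.60 (A.2) | 0.70 kept | 356 | 43% |
| 0.66 (Section 1) | 0.70 kept | 2,134 | 11% |
| 0.60 | 0.78 (18 points kept) | 103 | 91% |
| 0.66 | 0.84 (18 points kept) | 90 | 95% |

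**6. Clustered outcome totals.** 2 x 225 = 450 and 2 x 282 = 564. A.4 and A.5.1 give 550, a gap of 14 women, or 2.5% of 564.

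**The case against.** The strongest reply is that the error does no harm. On the stated rates the sample is too large, unclustered power at 180 agrees with the anticipated figure above 90%, and the expected 550 women exceed both 288 and 360. This stands as far as it goes. A reader might infer from the wrong n that the trial is underpowered; this arithmetic does not show that, and correcting it alone does not make power less favourable. What remains is that a stated figure is wrong and that two totals stand for one component.

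A reader might also infer that 60% and 66% disprove 0.52. The documents do not support that. The 0.52 is credited to pilot studies in the investigators' own community, the 60% is offered as a belief about the region, and the 66% is a cited figure for rural Kabale. Local communities may lie below a wider average. Nor does the protocol say that the 48-woman ultrasound programme of March 2013 was the source of 0.52, so features of that programme cannot be held against the rate. The large figures, 356 and 2,134, arise only if the target stays at 0.70 while the control rate rises. Keeping the 18-point difference lowers the requirement instead. What stands is a request to reconcile the three values.

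Finally, 550 against 564 may be simple rounding, and A.5.1 asks only for an expected number.

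**Conclusion.** The point holds in limited form. The 144 in A.5.4 item 1 is wrong for the inputs given: they require 115 per group, or 125 with continuity correction. This rests only on the protocol's own inputs and no standard variant at the stated alpha and power changes it. The 288 v 360 conflict between A.4 and A.5.4 is equally firm.

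The cause is not determined. Double use of the 25% allowance needs no figure from outside the protocol; a control rate of 0.54 also fits exactly. The choice decides whether the right inflated total is 288 or 360, and whether 180 per group reaches 90% power (94% with 0.52, 88% with 0.54). In the second case the anticipated power could still be met if enrolment exceeds 180, as item 1 expects, but not at 180 itself.

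All power figures here ignore clustering, as item 1 does. Whether it should do so in a community-randomised trial is a separate matter. The control-rate inconsistency is real but soft, and 550 v 564 is minor.

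**What to change.** 1. In A.5.4 item 1, state the control rate actually used and the uninflated n that follows: 115 per group for 0.52 (or 125 if a continuity correction is intended, and say so).
2. Apply the 25% allowance once. By the protocol's own multiplication, 0.52 gives 144 per group and 288 in total. If 0.54 was the rate used, correct the rate; the figures are then 144, 180 and 360, and the power statement must be revised for 180 per group.
3. Use that one total in A.4 and A.5.4. Settle it before any design effect is applied.
4. Add a sentence reconciling the pilot-based 0.52 with the 60% in A.2 and the 66% in Section 1. Show power at those control rates both with 0.70 kept (43% and 11% at 144 per group) and with the 18-point difference kept (91% and 95%), and say which effect is intended.
5. Align 550 and 564 across A.4, A.5.1 and A.5.4.

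The cost is a short recalculation and changes of wording. On the stated rates, no additional women are needed for this correction alone.

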One of the greatest barriers to maternal health is geography and distance from regional centers where maternal health services are provided. The population in Kabale is situated in smaller, rural communities scattered across a geographically mountainous region. As the majority of rural communities are lacking healthcare centers and trained professionals, pregnant women can only receive trained maternal healthcare services outside their communities. However, the distance from their local communities to the regional center where the government hospital and Kigezi Healthcare Foundation’s (KIHEFO) medical and maternity center are currently operating is immense. As a result, the majority of subsistence agriculture households cannot afford the cost to travel to regional centers for antenatal, natal and postnatal care.

Cultural attitudes surrounding childbirth, mainly the fear and stigma of receiving maternal healthcare outside home communities, is also problematic to providing pregnant women with professional medical healthcare services, and overall, reducing maternal mortality. This cultural fear is generated largely by a lack of education amongst rural populations in understanding the additional risks associated with childbirth due to realities of poverty, malnutrition, disease and illness. As a result, many pregnant women who are living in rural communities maintain the preference to give birth at home, despite lacking access to trained birth attendants who can respond to high-risk complications that arise, and facing high rates of maternal mortality.

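### The delivery-preference outcome is sized on unsourced near-ceiling rates (0.95 v 0.85) that are hard to reconcile with the Background, and its 80% power depends on them and on a design effect the protocol does not state

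*Protocol*

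**What the plan says.** Section A.5.4 treats delivery preference as one of two primary outcomes with a sample size. Item 2 opens with "Patient-level outcomes (clustered): At a two-sided alpha of 0.05 and holding power at 80%, using an estimated intracluster coefficient (ICC) of 0.1" and continues "with p1 of 0.95 and p2 of 0.85, and an average cluster size of 60 pregnant women (m"). The result is: "then 225 pregnant women will be required per study arm, which is equivalent to needing 4 clusters per group". After the non-response allowance, "Inflating this by 25% to account for potential non-response gives 282 pregnant women per group". The section says of clustering: "In this case a design effect is added to account for the clustering for this patient-level outcome", and its second note confirms the ICC: "we have used 0.1 in our calculations".

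The first note attributes the antenatal-uptake rate to pilot work. The second concerns only the ICC. Neither covers 0.95 or 0.85.

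The Background (section 1) describes the region differently. It reports that "only 30% of births in Kabale take place in health centers, with most births occurring at home", and says that "many pregnant women who are living in rural communities maintain the preference to give birth at home", without a percentage. Objective A(iii), in A.3 and again in section 2, is to improve preference for delivery with medical professionals.

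**The concern.** For a binary outcome the assumed rates fix the variance, p(1-p), and so the sample size. Rates of 0.95 and 0.85 lie near the ceiling, where the variance is small and a 10-point difference is cheapest to detect. Read as the control rate, 0.85 leaves only 15% of women not preferring a facility. That fits poorly with a Background that presents preference for home birth as a main obstacle, and with an objective built on changing it.

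If the true control rate is lower and the difference of interest is still 10 points, 225 women per arm give much less than the stated power. A null result on a primary outcome could then be read as evidence of no effect when the trial had little chance of finding one.

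**Working it through.** **Inputs.** From A.5.4, item 2: two-sided alpha 0.05, power 80%, rates 0.95 and 0.85, m = 60, ICC 0.1, 225 women and 4 clusters per arm. The protocol does not label p1 and p2. A.7.1 compares the arms with control as reference, so I take 0.85 as the control rate. Control rates below 0.85 are my assumptions.

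**1. The plan's own figure.** Before clustering, with mean rate 0.90:

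n = [1.960 × √(2 × 0.90 × 0.10) + 0.842 × √(0.95 × 0.05 + 0.85 × 0.15)]² / 0.10² = (0.832 + 0.352)² / 0.01 = 140.1, so 141 per arm.

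The stated ICC and cluster size give a design effect of 1 + 59 × 0.1 = 6.9. Then 141 × 6.9 = 972.9, so 973 women per arm, or 17 clusters of 60. The figure 225 is not reproduced this way. It is matched by 141 × 1.59 = 224.2, rounded up, and 1.59 = 1 + 59 × 0.01 is the design effect for an ICC of 0.01.

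**2. Power at 225 per arm for a 10-point difference.** With V = p1(1-p1) + p2(1-p2) and design effect D:

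power = Φ(0.10 / √(V × D / 225) − 1.960)

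For 0.95 v 0.85, V = 0.0475 + 0.1275 = 0.175. With D = 1.59 the ratio is 0.10 / 0.0352 = 2.84, so power = Φ(0.88) = 81%. With D = 6.9 the ratio is 0.10 / 0.0733 = 1.37, so power = Φ(−0.59) = 28%.

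| Control rate | V | n per arm before clustering | Power, D = 1.59 | Power, D = 6.9 |
|---|---|---|---|---|
| 0.85 | 0.175 | 141 | 81% | 28% |
| 0.80 | 0.250 | 199 | 66% | 21% |
| 0.70 | 0.370 | 294 | 50% | 15% |
| 0.60 | 0.450 | 356 | 43% | 13% |
| 0.50 | 0.490 | 388 | 40% | 13% |
| 0.30 | 0.450 | 356 | 43% | 13% |

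Using the pooled variance under the null lowers each power by about one point or less. The normal approximation makes no allowance for having only 4 clusters per arm, so all of these figures are optimistic.

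**3. Dependence on the effect scale.** The table holds the absolute difference at 10 points. From a control rate of 0.30:

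- Same odds ratio, (0.95/0.05) / (0.85/0.15) = 3.35: the comparison becomes 0.59 v 0.30 and needs only 46 women per arm before clustering. Power at 225 is above 99% with D = 1.59, and 66-69% with D = 6.9 depending on the variance form.
- Same relative risk, 0.95 / 0.85 = 1.118: the comparison becomes 0.335 v 0.30 and needs 2,731 per arm before clustering. Power at 225 is about 9% with D = 1.59.

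**4. What the Background figures measure.** The 30% is the actual place of birth among all Kabale births. The sized outcome is stated preference among pregnant women who come to a camp. The sentence on preferring home birth concerns the right quantity but gives no number. No section gives a local percentage for stated preference among attenders.

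**The case against.** The strongest reply is that nothing in the protocol contradicts 0.85, and this stands. A reader might infer from the 30% figure that the control rate is wrong and the variance therefore understated. The documents do not support that. Place of birth is behaviour, and the Background also attributes low facility use to distance and to travel costs that most households cannot meet. Women who choose to attend a camp are a selected group. Low facility births and a high stated preference among attenders can both be true.

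The rate may also be a post-camp one. A.5.4 speaks of preference before and after the clinic, A.4 describes a pre-clinic questionnaire and A.6.1 lists an exit survey. Control women attend the same kind of camp and are offered the same ultrasound, since only the advertising differs. A post-camp rate of 0.85 would conflict less with a Background that describes women before any camp.

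A reader might also infer that the choice of control rate is what costs the trial its 80% power. That does not hold either. At the protocol's own rates, ICC and cluster size, power is already about 28%, so the larger and demonstrable fault is the design effect. The direction of the rate's influence also depends on the scale: at a constant odds ratio a lower control rate needs fewer women. That case, however, requires a 29-point shift produced by advertising wording alone, and A.7.1 names the relative risk as the effect measure. On that scale the loss is greater than in the table.

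What remains is that the rates have no source, although item 1 of the same section sources its own, and that the power claim is sensitive to them.

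**Conclusion.** The point holds as a lack of support for the rates, not as proof of a wrong rate. The pair 0.95 v 0.85 is unsourced and hard to square with the protocol's account of home-birth preference, and less directly with the 30% facility births.

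Under the design effect implied by 225, moving the control rate only from 0.85 to 0.80 takes power from about 81% to 66%, so the sensitivity does not require a rate near 30%. Under the stated ICC and cluster size, power is about 28% at 0.85 and 13% at 0.30-0.60. The unqualified 80% is therefore unsupported whichever rate is right.

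These figures assume a fixed 10-point difference, 225 women per arm analysed, p2 as the control rate and a normal approximation. The point is secondary to the design-effect discrepancy, but it would remain after that is corrected.

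**What to change.** In A.5.4, item 2:

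- Say whether 0.85 is a pre-camp or post-camp rate and in which arm it applies, and give its source.
- Withdraw the unqualified 80% claim. For the planned number of communities, state the power or the smallest detectable difference over control rates of about 0.30 to 0.85, using the stated ICC and cluster size and naming the effect scale held fixed.
- Add a sentence reconciling the chosen rate with the Background, for example by separating stated preference among attenders from actual place of birth. The Background itself need not change.

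The cost is one rewritten paragraph and a less favourable stated power. No extra enrolment is needed.

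### The clustered sample size (225 women, 4 clusters per arm) does not follow from its own inputs: at ICC 0.1 the design has about 22–29% power, not 80%

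*Protocol*

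**What the plan says.** Protocol A.5.4 sizes two outcomes. Item 2 covers the patient-level outcome, preference for delivering in a health facility, and the introduction to A.5.4 says that a design effect has been included for it. The assumptions are introduced as "At a two-sided alpha of 0.05 and holding power at 80%, using an estimated intracluster coefficient (ICC) of 0.1", with proportions 0.95 and 0.85. The result is "an average cluster size of 60 pregnant women (m), then 225 pregnant women will be required per study arm", which the protocol equates to 4 clusters per group. It then adds: "Inflating this by 25% to account for potential non-response gives 282 pregnant women per group".

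Note 2 under the calculation confirms the ICC ("we have used 0.1 in our calculations") and places it in a wider range: "process outcomes (which our research is studying) range from 0.05 to 0.15".

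A.4 carries the total forward as "randomized clusters (sample size of 550", and the participant table in A.5.1 also enters 550. Section 7 (Statistical Design) confirms that communities are the randomised unit. A.7 analyses delivery preference between arms with GEE and an exchangeable correlation structure.

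**The concern.** With 60 women per cluster, an ICC of 0.1 is a heavy penalty: the required size should rise nearly sevenfold over individual randomisation. A total of 225 per arm is too small to contain that penalty, although the protocol says it was applied. Four clusters per arm is also few enough that the number of clusters, not the number of women, limits the information.

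At stake is the power claim for an outcome that A.5.4 lists among the primary ones. If the trial finds no difference in delivery preference, a reader who trusts the 80% would take that as evidence against the planned 10-point effect, when the trial had little chance of detecting it.

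**Working it through.** **Inputs, all from A.5.4 item 2 and its note 2.** Two-sided alpha 0.05 (z = 1.960); power 80% (z = 0.842); p1 = 0.95, p2 = 0.85; ICC = 0.1, range 0.05–0.15; average cluster size m = 60; equal arms. The protocol gives no design-effect formula, so the standard 1 + (m − 1) × ICC is assumed.

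**1. Size without clustering.** With mean proportion 0.90 and V = 0.95 × 0.05 + 0.85 × 0.15 = 0.175:

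n = [1.960 × √(2 × 0.90 × 0.10) + 0.842 × √0.175]² / 0.10² = 140.1, so 141 per arm.

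**2. Trying to reproduce 225.** Design effect = 1 + 59 × 0.1 = 6.9.

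- 140.1 × 6.9 = 967 women per arm (973 if 141 is used).
- 967 / 60 = 16.1, so 17 clusters per arm.

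Other ways of computing the unclustered size do not help:

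| Method | Unclustered n per arm | × 6.9 |
|---|---|---|
| Pooled variance | 141 | 973 |
| Unpooled variance | 138 | 953 |
| Continuity-corrected | 160 | 1,104 |
| Arcsine | 133 | 918 |
| One-sided | 109–111 | 753–766 |

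At ICC 0.05, the most favourable end of the protocol's range, the pooled figure is 557 and the smallest variant (one-sided) is 431. None of these gives 225.

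**3. What 225 implies.** 225 / 141 = 1.596, so the ICC is 0.596 / 59 = 0.0101. Working forward with ICC 0.01: 141 × 1.59 = 224.2, rounded up to 225; 224.2 / 60 = 3.74, rounded up to 4 clusters. Both stated results are matched exactly by an ICC ten times smaller than the one stated.

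**4. Power of the stated design.** Four clusters of 60 give 240 women per arm. At ICC 0.1:

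- effective n = 240 / 6.9 = 34.8 per arm
- SE of the difference = √(0.175 / 34.8) = 0.071
- 0.10 / 0.071 = 1.41 standard errors
- power = Φ(1.41 − 1.96) = 29%; with a noncentral t on 2 × 4 − 2 = 6 df, 22%

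| Per arm | ICC | Design effect | Effective n | Power, normal | Power, t |
|---|---|---|---|---|---|
| 4 × 60 | 0.05 | 3.95 | 60.8 | 46% | 35% |
| 4 × 60 | 0.10 | 6.90 | 34.8 | 29% | 22% |
| 4 × 60 | 0.15 | 9.85 | 24.4 | 22% | 17% |
| 4 × 70.5 (= 282) | 0.10 | 7.95 | 35.5 | 30% | 22.5% |
| 5 × 60 | 0.10 | 6.90 | 43.5 | 35% | 28% |
| 16 × 60 | 0.10 | 6.90 | 139.1 | 80% | 78% |
| 17 × 60 | 0.10 | 6.90 | 147.8 | 83% | 80% |

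**5. Ceiling.** As m grows, the effective n for k clusters tends to k / ICC. For 4 clusters at ICC 0.1 that is 40 per arm, which gives at most about 33% power (normal approximation).

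**6. Precision.** At 4 × 60 and ICC 0.1, the 95% interval half-width for the difference is 1.96 × 0.071 = 14 points, or 17 points with t on 6 df (2.447 × 0.071). The target difference is 10 points.

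**7. Totals.** 225 × 1.25 = 281.25, so 282 per arm and 564 in all, against 550 in A.4 and A.5.1. Four clusters at the assumed size hold 240 per arm; reaching 282 takes either a fifth cluster or about 70.5 women in each of four.

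**The case against.** The strongest reply is that 22–29% assumes an unadjusted comparison between arms at one time. A.5.4 describes the outcome as a change around the clinic visit, there are pre-clinic and exit surveys, and randomisation is stratified by catchment size, so an analysis using baseline responses or strata could reduce the between-cluster variance. That is true in principle. However, the stated calculation uses two proportions and an ICC with no within-woman correlation, and A.7 does not specify adjustment for baseline preference. It cannot explain 225. The 22% end also depends on a t reference with 6 df, which A.7 does not specify; without it the figure is 29%.

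A.4 speaks of patient-level randomisation for delivery preference, which would remove the design effect. But A.5.4, A.7 and Section 7 all treat this outcome as clustered, and the messages are given to whole communities.

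On the consequence, A.8 names attendance as the primary objective, and A.7 promises confidence intervals, so imprecision would be visible to a careful reader. This softens the harm but leaves a wrong power statement for an outcome that A.5.4 calls primary.

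On the totals, 60 is an average and 282 includes an allowance for non-response, so 240 and 282 need not conflict if clusters run larger than 60. The mismatch that remains in the protocol's own figures is 564 against 550, which is minor.

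Finally, use of an ICC of 0.01 is inferred from the exact match; the protocol does not say so. The finding does not depend on it.

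**Conclusion.** The concern holds. The stated inputs require about 970 women and 17 clusters per arm, roughly four times the 225 women and 4 clusters given. With 4 clusters of 60 per arm at ICC 0.1, power is 29% (normal) or 22% (t, 6 df). Over the protocol's ICC range of 0.05–0.15 it runs from 46% down to 22% (normal), or 35% down to 17% (t). Enrolling the inflated 282 in the same four clusters leaves it at 30% or 22.5%.

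These figures assume the standard design effect, equal cluster sizes and an unadjusted between-arm comparison. No ICC in the protocol's range brings 4 clusters of 60 near 80%. This must be fixed, because the protocol claims a power that its own assumptions contradict.

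**What to change.** Correct A.5.4 item 2 so that the inputs and the result agree:

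- Show the steps: 141 per arm unclustered, design effect 6.9, about 970 women and 17 clusters per arm for 80% power, before any allowance for non-response.
- If the trial stays at 4 clusters per arm, delete the 80% claim. State power as about 22–29% at ICC 0.1, with the results at 0.05 (35–46%) and 0.15 (17–22%), and the expected interval half-width of 14–17 points. Present delivery preference as an estimate with its confidence interval, not as a powered test.
- If a smaller ICC was intended, note 2 must say so and justify a value below the range it now cites.
- State the number of clusters and the expected cluster size behind 282, and make the totals in A.4 and A.5.1 (550) agree with A.5.4 (2 × 282 = 564).

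Restating the power is a wording change and needs no extra women; the cost is a much less favourable stated power. Actually reaching 80% would mean 13 more clusters per arm.
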